### Demographic/clinical variables/covariates

As a control parameter, the ‘Hospital Anxiety and Depression Scale’ (HADS) will be administered exploring symptoms of anxiety and depression [49]. We will also measure patient-reported disability of pwMS using the ‘Patient Determined Disease Steps’ (PDDS) [50]. The ‘Stage of Decision Making’ [51] questionnaire asks for the patient’s readiness to engage in decision-making, progress in decision-making, and susceptibility to considering or re-considering options. It may be useful in screening out pwMS who may not benefit from decision aid interventions.

For a list of outcomes and a schedule of assessments, see Table 1.

**Table 1 Tab1:** Study assessment

	Study period			
	Enrolment	Pre-study baseline/allocation	Study/post-allocation	
**Timepoint**	***−t***_***1***_	**0**	***t***_***1***_	***t***_***2***_
**Enrolment:**				
**Eligibility screen**	X			
**Informed consent**	X			
**Randomisation**		X		
**Sociodemographic data and MS-related data**		X		
**Assessments**				
**PDDS**		X		
**HADS**		X	X	
**DSES**		X	X	
**PrepDM**			X	
**RIKNO**		X	X	
**MMIC**		X	X	
**SURE**		X	X	
**CPS**		X	X	
**PAM 13-D**		X	X	
**Affective forecasting**		X	X	
**Social support**			X	
**Stage of decision making**		X		
**eHIQ-Part 1**		X		
**eHIQ-Part 2**			X	
**Patient treatment decision/Uptake**				X

*t1* after 4 weeks usage of intervention or comparator website(s), *t2* after physician encounter

### Participant timeline

Figure 2 shows the flow of enrolment, interventions, assessments, and visits for pwMS.

**Fig. 2 Fig2:**
[figure not shown]
Study flowchart

### Sample size

To our knowledge, there is no previous research using decision aids with patient narratives and addressing decision self-efficacy. However, since the main aim of the pilot RCT is not to give a formal assessment of efficacy, but rather to evaluate trial procedures and processes as well as to get estimates of parameters for the main RCT sample, the sample size justification is based on rules of thumb for pilot RCTs as given by Sim and Lewis. The authors recommend for a two-armed pilot RCT a total sample size of 55, which would minimise the overall sample size for the main RCT for small to medium standardised effect sizes [52–54]. Additionally, pilot RCTs on decision support tools in MS showed comparable sample sizes [31, 55].

### Recruitment

Participants will be recruited by 2–3 neurological practices, clinics, or rehabilitation centres in Germany. Potential participants will be invited to read the patient information sheet before deciding whether to take part in the study. Informed consent will be obtained by a physician or trained scientific personal in the participating neurological practices, clinics, or rehabilitation centres.

Once consent has been obtained, participants will get a link and an individual access key to the study registration webpage, which is QuestBack Unipark (2019), an online survey tool. There, participants will be asked for socio-demographic and MS-related data.

## Assignment of interventions

### Sequence generation

PwMS will be randomly allocated in blocks with variable block length at a 1:1 ratio to the intervention or the control group. The concealed allocation sequence will be computer-generated by the randomisation sequence of QuestBack Unipark.

### Concealment mechanism

The randomisation will be automatically performed via QuestBack Unipark and will be therefore concealed.

### Implementation

PwMS will be enrolled in the participating neurological practices, clinics, or rehabilitation centres. The allocation sequence and participants’ assignment to interventions will be automatically generated by QuestBack Unipark.

### Blinding

Blinding of the pwMS is pursued but is only possible to a limited extent due to the type of intervention. We will explain in our information and consent form that we intend to assess whether pwMS find different health information websites helpful on a range of self-reported outcomes. Researchers involved in study recruitment, administration of interventions, and data analysis will be blind to the allocation of intervention and control group. Since we do not expect relevant adverse events, no procedure for unblinding is planned.

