## Methods

### Trial design

The PExMS project follows the guidance of the Medical Research Council [30] for the development and evaluation of complex interventions and adheres to the SPIRIT checklist (see Additional file 1). The process has a development as well as a feasibility and piloting phase.
Development: The PExMS website was developed within a qualitative interview study, where PEx were collected (see ‘Intervention description’).Feasibility and piloting: First, people with RRMS (see ‘Intervention description’) will be asked about their experiences with the PExMS website (e.g. usability, acceptance, layout, navigation) and the outcome measurement procedures.Second, in a two-arm pilot RCT, we will compare a combination of the PExMS website and evidence-based patient information with evidence-based patient information alone. The pilot trial is intended to test recruitment, outcome measures, data collection (sampling and timing), randomisation procedures, and acceptability of the intervention for pwMS and practitioners, and gain exploratory results that could be used for sample size estimations in future RCTs. We want to assess whether the intervention was conducted as intended (fidelity) and assess the quantity of the implemented intervention (dose).A mixed-methods process evaluation will be applied. In the recruitment phase, we will perform semi-structured telephone interviews with all responsible persons in participating centres to assess perceptions of strengths, weaknesses, risks, and opportunities of the study.After completing the study, centres which succeeded in recruitment and centres that dropped out prematurely or failed in recruitment will be interviewed and will be asked to fill out a process evaluation questionnaire to assess acceptability of the recruitment, randomisation and consent procedure, and the intervention itself.Additionally, approximately 10 patients, namely maximum users and minimum users, of the PExMS-website and those having dropped out will be interviewed in each group and will be requested to complete a process evaluation questionnaire.

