## Interventions

### Explanation for the choice of comparators

The control group will receive access to the DECIMS (Decision coaching in MS)-Wiki (www.wiki2.kkn-ms.de), an evidence-based patient information website focusing on MS immunotherapies for 4 weeks. DECIMS-Wiki is considered to provide excellent factual information with figures, but without PEx and is regarded as the gold standard. Further information is described elsewhere [31]. Site visits will be recorded and tracked with the explicit consent of the participants. At the end of the 4-week period, study participants will be invited to complete follow-up questionnaires.

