#### The intervention group

The intervention group will receive access to the PExMS website and the DECIMS-Wiki for 4 weeks. As in the control group, the site visits are tracked. At the end of the 4 weeks, pwMS will be invited to complete follow-up questionnaires.

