### Strategies to improve adherence to interventions

All participating neurological practices, clinics, or rehabilitation centres will receive a study folder including all relevant documents. Also, regular phone calls and telephone conferences will be conducted for arising questions and updates and for sharing experiences.

Usage of the intervention will be monitored by tracking the site visits. PwMS will be contacted by regular email reminders by a member of the coordinating centre to use the intervention. In case of non-use, participants will be reminded by email or telephone.

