### Confidentiality

All data collected during the study will be kept strictly confidential. All electronic data from the pilot RCT will be pseudonymised and there will be no possibility to link data to persons without access to the code list. Through the personal access of patients to the PExMS website or DECIMS-Wiki based on a personal account (sent via email), it will be possible to individually track the use of the websites (e.g. frequency, use of different parts), which will be used to analyse user behaviour and the feasibility of the study design. User’s IP address will be stored by the system but shielded to anyone but the system administration. A personal account name will be used to connect users and pseudonyms.

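### The blanket blinding statement cannot hold for staff who track PExMS use, interview users chosen by PExMS use, or analyse usage; blinding should be stated role by role

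*Protocol article*

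**What the plan says.** The Blinding section makes two statements. On participants it is candid: "Blinding of the pwMS is pursued but is only possible to a limited extent due to the type of intervention". On staff it is unqualified: "Researchers involved in study recruitment, administration of interventions, and data analysis will be blind to the allocation of intervention and control group".

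Other sections of the protocol article describe what staff do:

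- **Arm content** (Interventions). "The control group will receive access to the DECIMS (Decision coaching in MS)-Wiki", whereas "The intervention group will receive access to the PExMS website and the DECIMS-Wiki for 4 weeks". Site visits are tracked in both arms.
- **Adherence** (Strategies to improve adherence to interventions). "PwMS will be contacted by regular email reminders by a member of the coordinating centre to use the intervention", and "In case of non-use, participants will be reminded by email or telephone".
- **Tracking** (Confidentiality). Through personal accounts "it will be possible to individually track the use of the websites", down to which parts are used. The account name links the user to the study pseudonym. The only item described as shielded is the IP address.
- **Interviews** (Trial design). About 10 patients are interviewed, "namely maximum users and minimum users, of the PExMS-website", together with drop-outs.
- **Outcomes** (Primary outcomes). How often and how long the intervention is used is part of the acceptability measure listed there.
- **Allocation** (Concealment mechanism; Implementation). The survey platform randomises and assigns automatically.
- **Questionnaire data** (Data collection and management). Participants complete the scales online. The export is checked by a statistician of the coordinating centre and analysed in pseudonymised form.

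**The concern.** The staff statement covers three functions and makes no exception. Two of them, administration of the interventions and data analysis, include tasks whose raw material is PExMS usage. Because the arms differ only in access to that website, someone doing those tasks cannot stay unaware of allocation.

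Three things are at stake.

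- The pilot is meant to estimate use, retention and response. The Analysis section sets targets of drop-out below 20% and more than 60% of patient-reported outcomes collected. Staff who know the arm and contact participants could influence these quantities.
- The Analysis section leaves a choice open: complete cases come first, and imputation follows only if it is judged necessary. Whether the person making that choice is masked therefore matters.
- A later full trial may carry the blinding statement over, and readers would credit it as it stands.

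**Working it through.** No arithmetic reproduces or refutes a blinding claim, and the article gives no figure for it. The check sets each staff task beside the statement.

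**Premise.** Control participants have DECIMS-Wiki; intervention participants have DECIMS-Wiki and PExMS. A visit to PExMS therefore implies the intervention arm. The converse fails: a log with no PExMS visit does not settle the arm, since an intervention participant may not have opened the site.

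1. **Recruitment.** Consent is taken at the centres, and assignment is made later by the platform. No task given to recruiting staff exposes the allocation. *Statement not contradicted.*

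2. **Monitoring use and following up non-use.** Acting on an individual's non-use requires looking at that individual's record. Whoever reviews these records sees PExMS visits for every intervention participant who has made one. A generic reminder to someone who has visited no site need not reveal the arm, but the monitoring that precedes it does so for others. *Statement cannot hold for whoever reads the logs.*

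3. **Selecting and interviewing patients.** Being ranked as a heavy or light PExMS user presupposes PExMS access, so selection on that basis identifies the arm. The interview about experience with the site reveals it again. *Statement cannot hold.*

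4. **Analysing PExMS usage.** These data exist in one arm only, so coded arm labels would not mask them. They belong to the primary feasibility outcomes and are thus a central part of the data analysis. *Statement cannot hold.*

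5. **ANCOVAs of DSES and the other questionnaire outcomes.** These use exported questionnaires. An analyst with coded arms and no usage or interview data could remain blind. Pseudonymisation does not achieve this by itself: it hides identity, not arm, and the account name connects usage to the pseudonym. The article neither says that this analyst is kept apart from usage data nor says the opposite. *Blinding possible, but not secured by the text.*

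**Count of participants concerned in step 2.** With 55 participants at 1:1, about 55 / 2 = 27.5, so 27 or 28, are in the intervention arm (assuming a near-even split; the block lengths are not given). A PExMS log entry can directly identify at most those who opened the site, that is, between 0 and about 28 people. This counts people whose arm is visible in the logs. It does not measure bias.

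**The case against.** The strongest reply is that this is a feasibility pilot with exploratory testing, that it admits participant blinding is limited, and that a journal article may leave separation of files and masked codes to the full protocol or analysis plan. That reply stands for the questionnaire analysis: silence on the mechanism there is not an error. It does not rescue the statement for monitoring, interviewing and usage analysis, because no division of staff would make those tasks blind.

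A reader might go further than the article allows in several ways:

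- *That no staff blinding exists.* Automatic allocation leaves recruitment blinding intact, and the ANCOVAs can still be masked.
- *That all 55 allocations are revealed.* An empty or Wiki-only log need not show the arm, and the article does not say that account types differ by arm.
- *That every efficacy outcome is self-reported and so exposed to staff contact.* Treatment uptake at t2 is assessed by a centre physician and documented by centre staff, and it feeds the choice dimension of the MMIC.
- *That prompting differs by arm.* The reminder rules draw no distinction between arms, and visits are tracked in both.
- *That the same people chase use and questionnaires.* Both sections mention only a member of the coordinating centre.
- *That eHIQ-Part 2 unmasks the analyst.* It is scheduled at t1 without restriction to an arm, and nothing shows that it reveals allocation.
- *That the interviews bias the scales.* They are described next to the steps that follow study completion. If that is their timing, they cannot alter answers already given.

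**Conclusion.** The staff blinding statement is wrong as written for three groups: those who monitor individual PExMS use and follow up non-users, those who select and interview patients by PExMS use, and those who analyse PExMS usage. It is not contradicted for recruiting staff. For the questionnaire ANCOVAs, blinding is achievable but not secured by the text.

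The conclusion rests on one assumption that the article itself supplies: PExMS access exists in the intervention arm only during the 4 weeks. The size and direction of any bias cannot be derived, and no differential contact is shown. The consequence is a claimed safeguard that the design only partly has. It should be corrected because doing so costs little and because the analyst still has a handling decision to make on missing data.

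**What to change.** Replace the single staff sentence with a statement by role:

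- Recruiting staff are unaware of the upcoming allocation.
- Staff who handle usage tracking, non-use follow-up, interviews and usage analysis are not blind.
- The statistician for DSES and the other questionnaire outcomes receives a coded-arm file without usage logs or interview and process data. That statistician completes the ANCOVAs, including the decision on imputation, before those data are merged.

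Send the reminders described under adherence in one arm-neutral text, and report the number of reminders per arm, so that any imbalance in contact is visible alongside retention and response.

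Cost: revised wording, one reminder text, a simple count, and a data export in two parts. The drawback is a less favourable blinding statement. Sample size, outcomes and schedule are unaffected.

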## Data collection and management

### Plans for assessment and collection of outcomes

Data from the Pilot RCT will be collected at four time points using web-based questionnaires from QuestBack Unipark (see ‘Outcomes’). This promotes the quality of data due to the avoidance of data entry and coding errors by third persons, reduced administrative burden, prevention of item nonresponse, and automatic application of skip patterns. Patients’ treatment decisions will be assessed after the intervention by a physician of the participating neurological practices, clinics, or rehabilitation centres and documented by physicians or study nurses of the study centre.

### Plans to promote participant retention and complete follow-up

PwMS will be contacted via regular email reminders by a member of the coordinating centre when it is time to fill in the questionnaires and will be asked to complete these within a specified period. Those who miss the completion will be reminded by email or telephone. PwMS who withdraw from the study will be requested whether they agree to continue to complete the questionnaires related to the primary and secondary outcomes.

### Data management

PwMS will enter their data in QuestBack Unipark. When the data collection is complete, it will be exported from QuestBack Unipark. The variables will be then renamed using a previously prepared codebook, and initial data checks will be conducted in IBM SPSS Statistics 25 by a statistician of the coordinating study centre. Pseudonymised data will be stored at the Institute of Neuroimmunology and Multiple Sclerosis at the University Medical Center Hamburg-Eppendorf. The analysis and usage of the data by the study principal investigator and his staff is done in pseudonymised form. The data collected during the study will only be made available for the scientific community in anonymised form. The same applies to the publication of the study results.

### Confidentiality

All data collected during the study will be kept strictly confidential. All electronic data from the pilot RCT will be pseudonymised and there will be no possibility to link data to persons without access to the code list. Through the personal access of patients to the PExMS website or DECIMS-Wiki based on a personal account (sent via email), it will be possible to individually track the use of the websites (e.g. frequency, use of different parts), which will be used to analyse user behaviour and the feasibility of the study design. User’s IP address will be stored by the system but shielded to anyone but the system administration. A personal account name will be used to connect users and pseudonyms.

## Analysis

The feasibility and process evaluation findings will inform the design of a future fully powered, randomised controlled trial to formally evaluate the effectiveness of the intervention. Therefore, we seek a drop-out rate < 20% and to collect > 60% of patient-reported outcomes (questionnaire response rate). Frequencies will be determined for categorical variables, and summary statistics (mean and standard deviation or median and quartiles, as appropriate) will be calculated for quantitative variables. Exploratory formal hypothesis testing using ANCOVA models will be performed since this is a pilot RCT. Estimated differences in outcome measures of efficacy adjusted for baseline values will be calculated. No interim analyses and stopping guidelines are planned. Initially, all analyses will be performed on complete cases. If necessary, sensitivity analyses will be conducted with imputed datasets derived by multiple imputation or mean value imputation.

Qualitative data gained through interviews will be managed using MAXQDA Analytics Pro 2018 and analysed thematically following Braun and Clarke [34].

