## Objectives

By embedding a process evaluation within the pilot trial, the primary study objective is to test the feasibility of an intervention using PEx as a supplement to evidence-based information to establish whether it is possible to carry out a large future RCT. The specific objectives are to determine the following:
Acceptability of recruitment, randomisation, and consent procedureAcceptability and feasibility of collecting reliable and valid data on primary and secondary outcomesAcceptability of the intervention and processes to participants and clinical staffSuitability of the intervention usedBarriers to adherenceExplore aspects of the trial design and conduct with a patient and public involvement group

We hypothesise that PEx may help pwMS in the decision-making process for or against immunotherapy or their different forms, respectively. Therefore, the secondary objectives are (1) to obtain pilot data on the likely difference between the intervention and evidence-based information alone regarding decision self-efficacy; (2) to inform the sample size calculation for the substantive randomised clinical trial; and (3) to control for potential bias caused by PExMS.

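### Mean value imputation should be removed as an optional sensitivity analysis: it understates the SD and does not validly check the complete-case result (minor)

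*Protocol article*

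**What the plan says.** The Analysis section of the protocol article sets the order of work: "Initially, all analyses will be performed on complete cases". It then adds a conditional second step, under which, if needed, "sensitivity analyses will be conducted with imputed datasets derived by multiple imputation or mean value imputation". The two imputation methods are joined by a plain *or*. The text does not say which would be used when, or whether the mean would be taken within arm or over both arms.

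The same section sets targets of less than 20% drop-out and more than 60% questionnaire response. The efficacy analysis is an exploratory ANCOVA with adjustment for baseline.

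Under Objectives, feasibility is primary. One of the secondary objectives is "to inform the sample size calculation for the substantive randomised clinical trial". The Sample size section also counts parameter estimates for the main trial among the pilot's aims.

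**The concern.** Multiple imputation and mean imputation are not alternatives of equal standing. Multiple imputation carries the uncertainty about the missing scores into the standard error. Mean imputation replaces each missing score with a constant, which adds nothing to the sum of squares but still counts towards the sample size. The SD therefore falls. Depending on which mean is used, either the standard error becomes too small or the arm difference is pulled towards zero.

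A sensitivity analysis should show whether the result survives a different, plausible assumption about the missing scores. Mean imputation offers no such assumption. Agreement or disagreement with the complete-case result would partly reflect the method itself. This matters somewhat more in a pilot, because spread and interval width are among the outputs that readers will use to plan the next trial.

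**Working it through.** **The plan's own figure.** The total of 55 is a cited rule of thumb ("The authors recommend for a two-armed pilot RCT a total sample size of 55"). The document gives no alpha, power, SD or numeric effect size, so 55 cannot be reproduced from it. It is not disputed here and serves only as *n*.

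**Inputs from the document.** *n* = 55; allocation "at a 1:1 ratio to the intervention or the control group"; ANCOVA adjusted for baseline. Missingness of 20% (11 of 55) lies at the edge of the drop-out target and 40% (22 of 55) at the edge of the response target. About 10% (5 of 55) is a milder case.

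**Assumptions, not in the document.** Baseline-outcome correlation 0.5; data missing completely at random; true SD set to 1. For the sizing illustration: two-sided alpha 0.05 and 80% power.

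**Step 1: SD.** With *r* scores observed and arm means filled in, the pooled within-arm variance is multiplied by (*r* − 2)/(*n* − 2).

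| Missing | *r* | Variance factor | SD factor |
|---|---|---|---|
| 10% | 50 | 48/53 = 0.906 | 0.952 |
| 20% | 44 | 42/53 = 0.792 | 0.890 |
| 40% | 33 | 31/53 = 0.585 | 0.765 |

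Ignoring arm, the factor is (*r* − 1)/(*n* − 1), which gives SD factors of 0.953, 0.892 and 0.770. The SD is thus about 5%, 11% and 23% too small.

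**Step 2: arm-mean imputation, standard error.** Relative to complete cases, the nominal SE is multiplied by √[(*r* − 2)/(*n* − 2) × *r*/*n*]. At 20% missing this is √(0.792 × 0.8) = 0.796. Approximate type I error is 2 × [1 − Φ(1.96 × 0.796)] = 2 × [1 − Φ(1.56)], about 12%.

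Simulated ANCOVA with 4,000 runs per setting:

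| Missing | Type I error, arm-mean imputation | Type I error, complete cases |
|---|---|---|
| 10% | 8.0% | 4.8% |
| 20% | 11.1% | 5.4% |
| 40% | 24.3% | 5.4% |

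At 20% missing, the mean reported SE under arm-mean imputation is 0.216, against an actual sampling SD of 0.272.

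**Step 3: overall-mean imputation, difference.** If a share *m* of each arm is set to the common mean, the expected difference becomes (1 − *m*) times the true one. At 20% missing, 0.8 × 0.50 = 0.40 (simulated 0.402). Type I error stays near 5%, because the estimate and its SE shrink together (sampling SD 0.221, reported SE 0.216). The SD shrinks as before (0.889).

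**Step 4: what would happen if these figures were carried forward.** Per-arm size is 2(1.960 + 0.842)²(SD/difference)². With a difference of 0.5 true SDs this gives 63 per arm.

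- *Shrunken SD, unshrunken difference* (what arm-mean imputation yields). At 20% missing, 50 per arm and true power about 71%. At 10%, 57 per arm and 76%. At 40%, 37 per arm and 58%.
- *Overall mean, both quantities taken from the imputed data at 20% missing.* The standardised effect is 0.40/0.89 = 0.449. Required size is multiplied by (0.50/0.449)² = 1.24, so it is about 24% too large, not too small.

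**The case against.** The strongest reply is that nothing in the plan depends on this step. Complete cases come first, imputation is conditional and labelled a sensitivity analysis, and multiple imputation is named before mean imputation. The testing is exploratory, and the Sample size section says that formal assessment of efficacy is not the main aim, so an inflated error rate in an optional analysis decides little. This stands, and it is why the point is minor.

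A reader might infer that the plan will bias the variance used to size the main trial and leave that trial too small. The document does not support this. It never says that the planning SD would come from an imputed dataset, and by default it would come from complete cases. Nor is the direction fixed, as step 4 shows.

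A reader might also take the complete-case sentence literally and conclude that retention, website usage and treatment uptake would be summarised in completers only. That over-reads it. The sentence follows the text on baseline-adjusted efficacy estimates, and the feasibility outcomes count withdrawn and lost participants by definition. Usage tracking needs consent, and uptake is recorded only after the physician encounter, so neither is known for everyone.

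Two defences of the wording are weaker. The choice between the methods may be settled in an analysis plan that is not shown, but the article itself names mean imputation as acceptable. The phrase could mean filling in single items within a scale, which would be milder. However, the text speaks of imputed datasets, and the data collection section says that the web forms prevent item non-response, so mostly whole questionnaires would be missing.

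**Conclusion.** The point holds as a minor flaw: the article names a faulty method as an acceptable sensitivity analysis. The SD shrinkage follows from simple algebra at *n* = 55 and, on average, needs only that scores are missing completely at random. The type I error of about 11% at 20% missing applies to arm-mean imputation only and also assumes a baseline correlation of 0.5. The shrinkage from 0.50 to 0.40 applies to overall-mean imputation only. The 20% and 40% cases lie at the limits of the plan's own targets; at 10% missing the SD loss is about 5%.

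The complete-case estimates are untouched. Harm to the main trial's sample size is conditional on someone carrying a mean-imputed figure forward, which the document does not plan.

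**What to change.** In the Analysis section, delete mean value imputation as an option. Keep multiple imputation as the sensitivity analysis, with arm and baseline values (including the baseline score of the outcome, where it is measured) in the imputation model. Add one clause stating that the SD for sizing the main trial will come from observed or multiply imputed data.

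The cost is a sentence. Multiple imputation is already in the plan and is available in standard software. The only downside is that intervals in the sensitivity analysis will be wider than mean imputation would give, which is correct.
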